Over the course of the past 6 years at Erasmus Sophia Children’s Hospital (Rotterdam, The Netherlands), approximately two-thirds (142/216) of parents of patients with metopic synostosis chose conservative treatment, while the remaining one-third opted for surgical treatment. None of the conservatively treated patients developed signs of increased intracranial pressure nor required craniofacial surgery. The choice of conservative treatment extends beyond its clinical consequences, influencing financial expenses associated with the management of patients with craniosynostosis. Although studies in the field of craniosynostosis have compared costs and established the cost-effectiveness of various surgical techniques,^29^,^31^ an evident gap exists in the literature concerning cost-effectiveness analyses comparing conservative and surgical treatments, particularly in patients with metopic synostosis.

Taking into account the sporadic occurrence of increased intracranial pressure and the overall tendency to have worse cognitive, behavioural and ophthalmologic outcomes even after surgery, the functional indication for surgical intervention for patients with metopic synostosis seems uncertain. In the existing literature, all outcomes following conservative treatment for patients with metopic synostosis are hard to determine due to small sample sizes, relatively short duration of follow-up and mild characteristics in the majority of the conservatively treated patients.^1426^,^28 32^ Therefore, a prospective cohort study with adequate follow-up is needed to determine if a conservative policy is as effective as surgical intervention. We present the study protocol for an observational cohort study on the effectiveness of a conservative policy compared with craniofacial surgery in metopic synostosis. This study presents a unique opportunity to assess differences in outcomes between conservatively and surgically treated patients with metopic synostosis in domains including intracranial pressure, vision, cognitive and behavioural functioning, impact on family and child, aesthetic outcomes and societal costs.

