### Power & sample size considerations

Due to the minimal extra time required from participants and parents, the inclusion rate is expected to be high and the loss to follow-up is expected to be low. Annually, around 50 new patients with metopic synostosis are referred to our centre, with an anticipated consent rate of 90% among parents, demonstrating their recognition of this observational study’s significance and their willingness to participate. In addition, within the first study year, children aged 1–3 years old will be included for follow-up with sufficient available retrospective data. Because at Erasmus Sophia Children’s Hospital, standard care for patients with metopic synostosis includes follow-up until the age of 18 years, drop-out rates are expected to be low. Inclusion will add up to 450 patients total.

A power calculation for the primary endpoint was performed using simulation. To obtain parameters for the simulation, a linear mixed model for age-adjusted SD scores of head circumference was fitted on existing data of children who underwent surgery. The model included a random intercept and (linear) slope for the child’s age at the time of the measurement to account for correlation between repeated measurements of the same child and to allow for child-specific trajectories. To take into account the non-linear shape of the children’s SD over time, a natural cubic spline with four df for age at the time of measurement was used in the fixed effects. The parameters from this model formed the assumption for the surgery arm in the power analysis simulation. For the conservative treatment arm, we assumed the SD at baseline follows the same distribution as in the surgery arm, but assumed linearly decreasing SD values over time. The rate of SD decrease in the conservative arm was increased over different simulation scenarios to find the most extreme scenario for which non-inferiority of the conservative arm could be shown with sufficient power.

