Each simulated data set contained 245 and 195 children in the conservative and surgery arm, respectively. The number of available observations at each measurement time decreased with increasing age, taking into account the sequential inclusion of children throughout the study period (and resulting differences in length of follow-up). The differences in SD scores between subsequent measurements were calculated and modelled using a random-intercept linear mixed model that had the treatment arm as the only fixed effect. The resulting parameter estimate for the treatment arm describes the difference in the yearly decline of SD score in the conservative arm compared with the surgery arm. Non-inferiority was defined as the lower bound of the 95% CI of the treatment effect estimate being larger than −0.5 SD.

Assuming an average yearly decline in head circumference SD score of −0.25 in the conservative arm resulted in 90% power to demonstrate non-inferiority of the conservative arm at a 2.5% one-sided significance, with a non-inferiority margin of −0.5 yearly SD difference.

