### Statistical methods

#### Primary outcome

The primary outcome measurement of the head circumference is transformed to an age-specific and sex-specific SD score, according to national norms. The yearly decline in head growth is chosen as the primary outcome since this continuous measure has more power, allowing us to adjust for possible confounders. This would not be possible when using binary outcomes with low prevalence (eg, presence/absence of papilledema at funduscopy). Non-inferiority with regard to head growth from 0 to 8 years (yearly difference in SD score) is determined using a linear mixed model adjusted for potential confounders (including severity of phenotype, sex, syndrome and parental factors) and comparing the lower bound of the 95% CI of the treatment effect estimate (conservative vs surgery) to the non-inferiority margin of −0.5 SD.

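### The stated 90% power was simulated for an unadjusted model, so it is not the power of the confounder-adjusted primary test and may be too high

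*Protocol article*

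**What the plan says.** The Protocol article specifies two different models.

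- **Power model** (Power & sample size considerations). Differences between successive SD scores were "modelled using a random-intercept linear mixed model that had the treatment arm as the only fixed effect", with 245 conservative and 195 surgical children. The decision rule was: "Non-inferiority was defined as the lower bound of the 95% CI of the treatment effect estimate being larger than −0.5 SD". The result is introduced by "Assuming an average yearly decline in head circumference SD score of −0.25 in the conservative arm", which "resulted in 90% power to demonstrate non-inferiority of the conservative arm at a 2.5% one-sided significance". The −0.25 scenario was found by steepening the decline until the most extreme case with enough power was reached.
- **Primary analysis** (Statistical methods, Primary outcome). The lower confidence limit that is compared with −0.5 comes from a "linear mixed model adjusted for potential confounders (including severity of phenotype, sex, syndrome and parental factors").

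The Study design and Interventions sections say that treatment is not randomised and that parents choose it. The power section states no allowance for confounding or for covariate adjustment.

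**The concern.** The confidence limit that decides non-inferiority comes from the adjusted model, but the printed power comes from the unadjusted one. In a randomised trial the gap would matter little, because covariates are then nearly unrelated to treatment and adjustment can hardly widen the interval. Here parents choose the treatment, and severity, syndrome and parental factors may well predict their choice. Adjusting for such covariates removes part of the contrast between arms and can raise the standard error.

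The article itself ties power to adjustment: the Primary outcome section justifies a continuous endpoint by its greater power, which makes confounder adjustment possible. Power under adjustment is the quantity it does not report. At stake is the stated limit of tolerable decline (90% power at −0.25 SD per year) in a study whose results are meant to update the national guideline.

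**Working it through.** **Inputs from the Protocol article.** Power 90%; one-sided 2.5%; margin −0.5 SD per year; assumed conservative-arm change −0.25 SD per year; 245 and 195 children.

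**Not in the article.** The variance components, the surgery-arm mean yearly change, the number of observations at each age, R2 (share of treatment choice explained by the confounders) and q (share of within-arm outcome variance they explain).

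**The plan's own figure.** The 90% cannot be rebuilt without the variance components, so it is taken as given and solved backwards. One-sided 2.5% and 90% power require the distance from the assumed effect to the margin to be 1.960 + 1.2816 = 3.2415 standard errors. If the surgery arm is flat (an assumption), the distance is 0.5 − 0.25 = 0.25. Then SE = 0.25/3.2415 = 0.0771. With √(1/245 + 1/195) = 0.0960, the implied SD of a child's mean yearly change is 0.0771/0.0960 = 0.80. If the surgery-arm mean is instead +0.10 or −0.10 per year, that SD is 0.48 or 1.13. The 90% is attainable but cannot be verified.

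**Effect of adjustment.** The variance of the treatment effect is multiplied by about (1 − q)/(1 − R2), so

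power = Φ(3.2415 × √((1 − R2)/(1 − q)) − 1.96).

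This does not depend on the surgery-arm mean. Worked case, R2 = 0.20 and q = 0: 3.2415 × √0.80 = 2.899; 2.899 − 1.96 = 0.939; Φ(0.939) = 82.6%.

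| Assumed R2 | q = 0 | q = 0.10 | q = 0.20 |
|---|---|---|---|
| 0.10 | 86.8% | 90.0% | 93.0% |
| 0.20 | 82.6% | 86.3% | 90.0% |
| 0.30 | 77.4% | 81.6% | 85.8% |

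Power is below 90% only when R2 exceeds q. A regression simulation with 245 and 195 children agreed with the formula to within about 1.5 points.

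**What such an R2 would take.** For one binary adjuster, R2 = (difference in proportions)² × π(1 − π)/(p(1 − p)), with π = 245/440 = 0.557. Suppose severe phenotype in 30% of conservative and 70% of surgical children (assumed). Then p = 0.557 × 0.30 + 0.443 × 0.70 = 0.477 and R2 = 0.16 × 0.2468/0.2495 = 0.16. With 30% and 60%, R2 = 0.09.

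**Effect on the tolerable decline** (surgery arm flat, q = 0). The decline with 90% power is −0.5 + 0.25/√(1 − R2). At R2 = 0.20 this is −0.5 + 0.2795 = −0.22 SD per year, against −0.25 as stated.

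**Power at a small true difference** (same assumptions). With a true difference of zero the distance to the margin doubles. Even at R2 = 0.40, Φ(2 × 3.2415 × √0.60 − 1.96) = Φ(3.06) = 99.9%.

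**The case against.** Four objections have weight.

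- **Direction.** A reader might infer that the adjusted interval must be wider and the 90% must be too high. The documents do not support that. Prognostic covariates reduce residual variance, and with R2 and q both at 0.10 power is exactly 90%. The q = 0 column is the unfavourable end: covariates that explained none of the outcome would not be confounders. That the score is already standardised for age and sex limits what sex can explain, but says nothing about severity, syndrome or parental factors. This stands, so the claim is only that the figure may be too high.
- **Severity by arm.** The Introduction's remark about "mild characteristics in the majority of the conservatively treated patients" describes earlier literature, not this centre, where 142 of 216 families chose conservative treatment. Severity by arm is not reported here. This stands, and the imbalances used above are assumptions.
- **Baselines.** The simulation sentence "we assumed the SD at baseline follows the same distribution as in the surgery arm" may look like a second fault. It is not a material one. The response is a difference between successive scores, so a shift in baseline level cancels. Simulated power at shifts of 0, 0.5 and 1 SD was 90.2%, 89.3% and 91.1%, which is noise.
- **Consequence.** The −0.25 scenario is a searched boundary, not an expected decline, and the final confidence interval will carry any variance inflation. It would be wrong to infer that the study is underpowered. This stands and limits the size of the point.

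None of this removes the mismatch. The article specifies both models and attaches the printed power to the one that will not be used for the decision. Further scenarios may exist in a fuller document, but the figure as printed carries no such qualification.

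**Conclusion.** The point holds as a mismatch between the stated power and the planned test. The 90% at −0.25 SD per year belongs to a model with no covariates and may be too high for the adjusted primary analysis. Over the assumed range of R2 from 0.10 to 0.30, power is about 87% down to 77% if q = 0 and 90% down to 82% if q = 0.10, with no loss where q is at least R2. With a flat surgery arm and q = 0, the decline carrying 90% power moves to about −0.22 SD per year at R2 = 0.20. These figures rest on the back-solved 90%, a child-level approximation to the mixed model, and values of R2 and q that the article does not give. The planned adjustment, the decision rule and the viability of the study are not in question.

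**What to change.** Rerun the existing simulation with treatment depending on the confounders, and fit the adjusted primary model with the same confidence-limit rule. Take the confounder distributions by arm from the centre's own children (142 conservative and 216 − 142 = 74 surgical in the Introduction) where they were recorded. The article does not say that severity or parental factors were recorded for these children, nor does it define the parental factors. Where data are lacking, use a stated range of R2 and q.

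Then, in Power & sample size considerations, replace the 90% with the adjusted-model power at −0.25, or state the decline at which the adjusted model has 90% power. The cost is one rerun, some work on confounder data, and one restated figure. Patient numbers, the analysis and the margin stay as they are. The downside is that the stated figure may be less favourable.

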##### Head circumference

The primary outcome is the change in head circumference, as head growth decline is an indicator for raised intracranial pressure. Head circumference is repeatedly measured every year from age 0–8 years. Measurements are performed manually with a measuring tape by skilled clinicians. Head circumference is defined in cm and corresponding SD based on national normative values. A decline in head circumference of more than 0.5 SD is considered clinically relevant. Head circumference is a significant predictor of intracranial volume, making it a very useful clinical measurement to monitor skull growth.^33 34^ As a non-invasive measurement accessible at every age, it serves as a valuable and efficient measurement to initiate further screening if abnormal in metopic synostosis patients.^7^ Patients with stagnation of the head circumference require further screening for raised ICP. Serial head circumference measurements, combined with a comprehensive screening protocol if necessary, provide a robust and clinically relevant approach to monitoring these patients. This method allows for regular, non-invasive assessment while minimising radiation exposure, which is particularly important in paediatric populations.

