#### Economic evaluation

An economic evaluation will be conducted from a societal perspective in accordance with the Dutch guidelines for economic evaluations in healthcare, in which healthcare costs, patient and family costs, and costs outside of the healthcare sector (ie, productivity costs of the parents related to paid work absenteeism) will be considered.^54^ The time horizon is 8 years to include all relevant costs and effects. The primary outcome (ie, head circumference) will be used as the effect measure in the cost-effectiveness analysis. The incremental cost-effectiveness ratio of surgery versus conservative treatment will be expressed as costs per case of decline in head circumference >0.5 SD.

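### The non-inferiority margin is 0.5 SD per year, but the protocol's threshold for a clinically relevant decline is 0.5 SD with no time unit, so a non-inferior verdict could coexist with a mean loss above that threshold

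*Protocol article*

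**What the plan says.** The figure 0.5 SD appears in four places in the protocol article.

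- **Outcomes, Head circumference:** "A decline in head circumference of more than 0.5 SD is considered clinically relevant". No interval is attached. The preceding text says that the head is measured every year from age 0 to 8.
- **Power & sample size considerations:** the treatment estimate "describes the difference in the yearly decline of SD score in the conservative arm compared with the surgery arm", so it is a rate. The section gives the decision rule as "Non-inferiority was defined as the lower bound of the 95% CI of the treatment effect estimate being larger than −0.5 SD" and then names the unit: "with a non-inferiority margin of −0.5 yearly SD difference".
- **Statistical methods, Primary outcome:** the effect is again a yearly difference in SD score over ages 0 to 8. The rule is printed without a time unit: "comparing the lower bound of the 95% CI of the treatment effect estimate (conservative vs surgery) to the non-inferiority margin of −0.5 SD".
- **Economic evaluation:** the effect measure is "costs per case of decline in head circumference >0.5 SD", and the time horizon is 8 years.

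The power section also describes how the planning case was found. The decline in the conservative arm was made steeper across scenarios until power was only just sufficient. That gave 0.25 SD per year with 90% power at one-sided 2.5%, from 245 conservative and 195 surgical children.

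**The concern.** The same number serves as a threshold for how much decline matters and as a margin on a yearly rate. If the threshold is an amount lost over follow-up, the margin allows that amount to be lost again each year.

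Head growth is the primary outcome because its decline signals raised intracranial pressure, and the article says that the results will be put into practice and into the Dutch guideline. What is at stake is the meaning of a positive primary result. A reader would take non-inferior to mean that conservatively treated children do not lose a clinically relevant amount relative to surgery, and the rule as written does not ensure that.

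**Working it through.** **Inputs from the article.** Margin −0.5 SD per year; planning decline −0.25 SD per year in the conservative arm; 90% power; one-sided 2.5%; 245 and 195 children; ages 0 to 8; threshold 0.5 SD.

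**Inputs not in the article.** The surgery-arm trajectory, the variance components and the number of observations at each age. The 90% therefore cannot be reproduced independently. It can only be used to infer the standard error (SE) that it implies.

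**1. SE implied by the stated power** (normal approximation). SE = (distance from the true difference to the margin) / (1.960 + 1.282).
- Surgery arm assumed flat: the true difference is −0.25, and SE = 0.25 / 3.2415 = 0.077 SD per year.
- Surgery-arm yearly change assumed between +0.05 and −0.10: the true difference runs from −0.30 to −0.15, the distance from 0.20 to 0.35, and the SE from 0.062 to 0.108.

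**2. The margin on the cumulative scale.** 0.5 × 8 = 4.0 SD extra mean loss relative to surgery if the difference is constant for 8 years, and 4.0 / 0.5 = 8 times the threshold.

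**3. The planning scenario on the cumulative scale.** 0.25 × 2 = 0.5 SD at year 2. 0.25 × 8 = 2.0 SD at age 8, and 2.0 / 0.5 = 4 times the threshold. This is the conservative arm's own mean change. The difference from surgery equals it only if the surgery arm is flat.

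**4. Worst observed difference that would still pass.** −0.5 + 1.96 × 0.0771 = −0.349 SD per year. Over 8 years that is −2.8 SD (−2.3 to −3.0 over the assumed range).

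**5. A margin that matches 0.5 SD over 8 years.** 0.5 / 8 = 0.0625 SD per year, for a constant difference only.
- Power at zero true difference with the SE from step 1: Φ(0.0625 / 0.0771 − 1.96) = Φ(−1.15) ≈ 12.5% (8% to 17% over the range).
- SE needed for 90% power: 0.0625 / 3.2415 = 0.019, about a quarter of 0.077.
- Sample size for 90% power at the implied SE: about 7,000 children (about 4,500 to 13,800 over the range).

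Steps 2 and 3 use only printed numbers. Steps 1 and 4 and the power and sample-size figures in step 5 depend on the assumed surgery-arm change.

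**The case against.** **The threshold may be yearly.** The sentence that defines it follows one about yearly measurement, so a visit-to-visit reading is open. On that reading the margin and the threshold share a scale, and the 8 years in the economic evaluation may be only the horizon for costs and effects. This stands in part: the article does not say that the 0.5 SD is a total. The cumulative reading is better supported, because the economic evaluation counts cases within 8 years and attaches no yearly unit. If a yearly threshold was meant, both sections would have to say so, and a sustained loss at the margin would still total 4 SD.

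**A child's threshold is not automatically a margin for arm means.** This is correct, and it is a reason for the protocol to justify the margin. The article reuses the number without an argument.

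**Multiplying by 8 assumes a constant difference.** The surgery arm is modelled with a spline, fewer children contribute at older ages, and follow-up ends at age 8 or in September 2030, whichever comes first. This stands, and the 4 SD figure carries that condition. The planning scenario depends on it less, because the article itself specifies a linear decline in the conservative arm.

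**Two stronger inferences fail.** A reader might infer that almost any data would pass. At the implied SE of 0.077, a true difference of −0.40 per year passes with probability Φ(0.10 / 0.0771 − 1.96) ≈ 25% (15% to 37% over the range), and one exactly at the margin passes with 2.5%. A reader might also infer that the study cannot show safety. The estimate and its interval may exclude smaller losses, papilledema is analysed separately, stagnating head growth prompts further screening, and an interim look at head growth is planned for 2025. The defect is limited to the non-inferiority verdict.

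**Conclusion.** The point holds for the primary decision rule. The margin is set on a yearly rate, the clinical threshold has no time unit and is used elsewhere as a case definition within an 8-year horizon, and the article does not connect the two.

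The planning case is the strongest evidence. The plan reports 90% power to declare non-inferiority when the average conservatively treated child loses 0.5 SD by year 2 and 2 SD by age 8. The 4 SD figure at the margin is correct arithmetic for a constant difference, but a true difference of that size would rarely pass.

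That the threshold means a total is the better-supported reading, not a stated one. If it is yearly, the inconsistency becomes an unstated unit and an unjustified margin, which still need correction.

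**What to change.** 1. State the time unit of the 0.5 SD threshold and reconcile four sections: Head circumference, Power & sample size considerations, Primary outcome, and Economic evaluation.
2. Define the primary contrast as the model-based difference between arms in cumulative change in head-circumference SD score to a stated age (age 8), with a time function that allows for the non-linear trajectory. Compare its lower 95% confidence limit with −0.5 SD.
3. If a yearly margin is kept, derive it explicitly from the cumulative threshold. The value 0.0625 SD per year applies only if the difference is constant over 8 years.
4. Rerun the existing simulation at zero true difference, report the surgery-arm trajectory and the variance inputs, and restate the power.

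**Cost.** An amendment and a rerun of existing code, with no new visits or data. With 90 of 450 children included by September 2024, the change can be made well before the final analysis. The real cost is power. It could fall to about 12.5% at the SE implied by the stated 90% with a flat surgery arm, and with about 50 referrals a year more recruitment could not make that up. If the SE is nearer 0.019, the present size would give about 90%. Only the simulation inputs can settle which applies.
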